### Recruitment

Recruitment will be staggered over 32 weeks and will include online recruitment through Facebook advertisements and Kijiji, an online classified message board, with offline recruitment through classified newspaper ads, and a Can $35 incentive for registering for the trial. Interested young adults will be referred to a website describing the trial. Potential participants will be screened at the entry webpage where their eligibility will be determined, informed consent will be sought, and registration for the trial will take place. A total of 1354 young adult smokers will be recruited. After providing informed consent and having completed the online baseline questionnaire, a computer-generated email message will be sent back to the participants confirming registration and participants will then be randomly allocated to either the control or intervention arm. The control group will participate in a usual care, self-help guide intervention called “On the Road to Quitting” [39] and the intervention group will participate in the Crush the Crave program.

### Randomization and Blinding

Participants will be allocated to intervention and control groups using a uniform 1:1 (control:intervention) allocation ratio and a computer-generated, simple randomization procedure. We will monitor the comparability between groups and, given the large sample size, the groups will be balanced based on three sources of variability with regard to smoking—sex, age, and cigarette consumption [40]. As documented in similar large trials, the likelihood is remote that, by chance, the two study groups may not be well matched for baseline characteristics [41-43]. Owing to the nature of the intervention, participants will be aware of the group to which they have been assigned. However, investigators and data collectors will be blinded to group allocation until completion of the trial.

### Study Intervention

#### Overview

The intervention group will receive a comprehensive and evidence-informed smoking cessation mobile phone app, Crush the Crave, via the Internet. Crush the Crave enables users to customize a quit plan by choosing a quit date and then deciding whether to quit immediately or reduce the number of cigarettes they smoke every week up to their quit date. Crush the Crave then assists smokers in staying on track by reminding them of how much money they have saved and how much their health improves over time after quitting. Based on contingency reinforcement, these milestones are tracked as rewards, which smokers can then choose to share with their social network via Facebook and Twitter, and rally support from friends and family. Participants can also link to the Crush the Crave Facebook community for additional support for quitting. Users of the app also receive supportive text messages tailored to their specific quit plan and where they are in the quitting experience. Crush the Crave will allow the intervention group to track their daily smoking habits and cravings as well as understand their craving triggers or psychosocial determinants by recording when, where, and why they were smoking. The app provides both graphic and tabular performance feedback (see Figure 2). The app also provides online distractions to help smokers deal with their cravings. There are social media tools, such as a YouTube channel and opportunities to chat with friends online to distract a user until the craving subsides a few minutes later. Evidence-based information is available for assisting participants during the quitting experience on topics such as relapse and dealing with cravings. Furthermore, data are collected in real time to both support the user and to track the usage of the app allowing for push notifications, helpful reminders, and ongoing data collection. Finally, Crush the Crave provides access to evidence-based cessation services such as smoking cessation quitlines and explains the benefits of, and dispels myths around, nicotine replacement therapy.

**Figure 2 figure2:**
[figure not shown]
Screenshots of the quit-smoking mobile phone app, CrushtheCrave.

#### Development of Crush the Crave

Crush the Crave was developed in early 2012 by a team of population health researchers, social media experts, and computer programmers as an evidence-informed, quit-smoking mobile phone and social media app for young adults aged 19 to 29. In addition to the input of key experts in the field of smoking cessation, development of the app incorporated Fiore’s practice guidelines for treating tobacco use and dependence [44] and principles of persuasive technology for behavior change [45]. The app was tested in March 2012 with eight focus groups consisting of 57 male and female young adult smokers on functionality, look and feel, and usability. Young adult smokers were engaged in the design and the naming of the app. Furthermore, the app was pilot-tested by over 300 smokers from April to June 2012. The pilot test revealed substantial engagement with 319 users triggering 7931 events, including 1444 visits to the quit help page, 1415 visits to the awards page, and 1016 visits to the progress tracking page. The focus groups of young adult smokers provided positive feedback on app functionality and content. In light of evidence that existing smoking cessation mobile phone apps are not developed by health professionals or academics, do not draw on behavior change theories or techniques, and do not have content aligned to clinical guidelines and other evidence-based practices [22,46], Crush the Crave is a relatively novel intervention in the area of smoking cessation.

### Standard Self-Help Condition

The control group will receive a standard, print-based self-help guide known as “On the Road to Quitting” [39] that has been recently developed by Health Canada for young adult smokers. This guide builds on an original guide that has been available for adult smokers for more than 10 years and includes evidence-based content for smoking cessation [47]. Participants will be able to both view and download the self-help guide via the Internet and can request a printed version of the guide. A print-based self-help guide was chosen as the control intervention because evidence from systematic reviews and meta-analyses of RCTs using printed self-help materials has demonstrated that there is no smoking cessation benefit from structured self-help printed materials [48-51].

Therefore, it has been determined that the effect of print-based self-help material is comparable to no treatment. In addition, a standard self-help control condition facilitates recruitment as it is problematic to offer participants a no-treatment option for a quit-smoking study.

### Data Collection

#### Baseline Questionnaire

Baseline data will be collected via a self-administered, online questionnaire completed by all consenting participants in both intervention and control groups. The baseline questionnaire will include the following demographic items: age, sex, ethnicity, marital status, education, income, and employment status. The following variables related to tobacco consumption will also be recorded: current smoking status, amount smoked, number and duration of past quit attempts, intentions to quit in the next 6 months, and the degree of nicotine dependence. Participants will also be asked a series of psychosocial questions, including beliefs and attitudes about quitting, self-efficacy or confidence in quitting, perceived stress and social support, and social norms related to smoking. Furthermore, participants will be asked about experience with mobile phone apps and self-help, use of NRT, and other cessation aids/supports, such as quitlines.

#### Questionnaire for 3- and 6-Month Follow-Up

Follow-up data will be collected from the same participants at 3 and 6 months in the same manner as the baseline questionnaire. In addition to the questions asked at baseline, participants will be asked core smoking status questions, including whether they have smoked any cigarettes or used other tobacco products, even a puff, in the last 30 days, 7-day point prevalence abstinence, number of quit attempts, and the reduction in cigarette consumption. Participants will then be asked questions on nicotine withdrawal, level of support received from friends and family for quitting smoking, additional cessation services that they sought for helping to quit, overall satisfaction with the app or self-help guide, use of the app or guide, opinions and beliefs about the app or guide, and challenges they experienced in quitting smoking. A modified Dillman method [52] for the online survey questionnaires will be used and up to 10 attempts (email and telephone) will be made to reach participants if they do not complete the online questionnaire within 2 weeks of the 3- and 6-month follow-up periods. Questionnaires will be pilot-tested with a convenience sample of young adult smokers.

### Outcome Measures

#### Primary Outcome Measure

The primary outcome measure will be self-reported, 30-day point prevalence abstinence from smoking at 6 months, operationalized as not having smoked any cigarettes, even a puff, or used other tobacco products in the last 30 days [53]. Biochemical validation of smoking status will not be done as a Cochrane Review of Internet-based interventions for smoking cessation found that very few studies used this method given the difficulties in obtaining samples [54]. In addition, accurate estimates of the prevalence of cigarette smoking among Canadians can be derived from self-reported smoking status data [55].

#### Secondary Outcome Measures

Secondary outcome measures are as follows:

1. The 7-day point prevalence abstinence at 6 months [53,56], the number of quit attempts (ie, how many times did participants stop using tobacco for 24 hours or longer over the past 6 months [57,58]), and the reduction in consumption of cigarettes [59].

2. Satisfaction, app utilization metrics, such as frequency of use and use of smoking cessation services (eg, NRT, health professional consults, medications, quitline counseling, and e-cigarettes).

3. Beliefs and attitudes, stress [59], social norms [57], behavioral intentions to quit smoking [58], degree of nicotine dependence and nicotine withdrawal [60], self-efficacy [61,62], and perceived social support [61,62].

Recent research on e-cigarette use has found the use of e-cigarettes is increasing rapidly, and research has found evidence of dual-use. Young adult smokers do not necessarily view e-cigarettes as cessation aids, as some consider them a complement and substitute for smoked cigarettes [63,64]. The prevalence of e-cigarette use amongst the cohort of young adult smokers, and the extent to which e-cigarette use mediates the primary outcome, will be investigated.

### Process Measures

For process measures, we will monitor downloading of the app and app usage via the tracking of events triggered when participants use the app (eg, connects with social support, seeks information on smoking, and tracks progress). For tracking, we will use Web-analytic data via Google Analytics and a secure database of app usage which records events triggered with a time stamp. For example, on a per-user basis we will track when a user logs into the app, number of user clicks on the “Smoke” or “Crave” buttons, and achievement of awards. Aggregate Google Analytics metrics will include visits, page view counts, and average time spent on a page.

To obtain a more in-depth understanding of the potential barriers to, and facilitating factors of, uptake of the mobile phone intervention, we will conduct semistructured interviews with a subsample of participants in the intervention group. To maximize variation (eg, age, sex, and level of satisfaction with the app), participants will be purposively recruited via email or telephone to participate. Sampling will be driven by saturation of themes. In keeping with previous studies [65], we anticipate the need to conduct approximately 40 interviews. Interviews will take place via telephone by a project team member with experience in qualitative interviews and will last 30 to 45 minutes. We will seek feedback on the app utilization, opinions and beliefs about the app, acceptability of the mobile phone intervention, participants’ specific likes and dislikes, and their perceived utility and satisfaction with each of the mobile phone intervention components. Interviews will be digitally recorded and transcribed. Interview transcripts and sociodemographic data will be entered as a project in the qualitative data software program, NVivo version 10. Study team members trained in qualitative methods will use an iterative process to understand the themes and key issues arising from the data.

### Sample Size and Power Calculations

Sample size calculations are based on a superiority trial [66,67] and are focused on the difference in the objective measure of the primary outcome event—30-day point prevalence abstinence from smoking—between intervention and control groups. Assuming a ratio of 1:1 for intervention to control subjects, an alpha of .05, power of 80%, and an effect size equal to a 50% increase in self-reported abstinence—17% in the intervention versus 11% in the control condition—the required sample size is 524 per group, for a total of 1048 participants using a two-tailed test on proportions [68]. The 50% increase in effect is reasonable and conservative based on trials of interventions using other mobile and Web-based technologies [41,69,70]. The estimated 11% abstinence rate in the control condition is based on the Ontario Tobacco Survey young adult smokers cohort study where in a sample of 592 young adult smokers, 68 (11.5%) were abstinent at the 6-month follow-up [71]. The 11% abstinence rate is what is expected to occur with a standard self-help condition and is similar to other trials that have tested the effect of self-help materials, with validated 6-month cessation rates of 5% to 15% [50,51]. Based on the experience of similar interventions [41,69], an overall estimate of 20% attrition translates into quit rates of 8.8% in the control condition and 13.6% in the intervention. Therefore, the total sample size required for each group is 677, for a total of 1354 participants.

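### The design effect is labelled and justified as a 50% increase in abstinence, but the rates that size the trial are a 54.5% increase; 80% power belongs to the rates, and an exact 50% increase has about 74%

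*Protocol article*

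**What the plan says.** Everything needed is in the protocol's Sample Size and Power Calculations section. With 1:1 allocation, alpha 0.05 and 80% power, the target is "an effect size equal to a 50% increase in self-reported abstinence—17% in the intervention versus 11% in the control condition". From this, "the required sample size is 524 per group, for a total of 1048 participants", "using a two-tailed test on proportions".

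The effect is then defended by its relative size: "The 50% increase in effect is reasonable and conservative based on trials of interventions using other mobile and Web-based technologies". The control rate is taken from a cohort study: "in a sample of 592 young adult smokers, 68 (11.5%) were abstinent at the 6-month follow-up", which is used as 11%.

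Finally, "an overall estimate of 20% attrition translates into quit rates of 8.8% in the control condition and 13.6% in the intervention", which gives 677 per group and 1354 in total. This dilution fits the Statistical Analysis section, where participants without a response count as smokers.

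**The concern.** One effect is described in two ways that do not match. A 50% increase over 11% is 16.5%, not 17%. Half a percentage point looks small, but the required sample size varies roughly with the inverse square of the difference, so it matters here.

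The mismatch also separates the effect that is argued for from the effect that is powered. The appeal to earlier trials is attached to the 50% figure, while the sample size follows from the larger 54.5% effect. A reader who takes the relative figure as the target will credit the design with an 80% chance of detecting a 50% increase. At the planning control rate that chance is about 74%, so the probability of missing such an effect is about 26% rather than 20%.

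**Working it through.** **Inputs** (all from Sample Size and Power Calculations): two-sided alpha 0.05 (z = 1.960); power 80% (z = 0.8416); 1:1 allocation; rates 11% and 17%; attrition 20%; 524 and then 677 per group; cited cohort rate 68/592 = 11.5%. The 50% is read as a relative increase in the proportion abstinent.

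**Step 1. Relative size of the stated rates.**
- 17/11 = 1.545, an increase of 54.5% (6 points).
- After attrition: 0.8 × 17% = 13.6% and 0.8 × 11% = 8.8%. The ratio is again 1.545, and the difference is 4.8 points.
- An exact 50% increase: 1.5 × 11% = 16.5%, or 1.5 × 8.8% = 13.2% after attrition.

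**Step 2. Reproduce the plan's figures.** The pooled-variance formula for two proportions, without continuity correction, is

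n per group = [1.960 × √(2p̄(1−p̄)) + 0.8416 × √(p₁(1−p₁) + p₂(1−p₂))]² / (p₂−p₁)²

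- 11% v 17%: p̄ = 0.14; (1.960 × 0.4907 + 0.8416 × 0.4889)² / 0.06² = 523.8, so 524. Matches the plan.
- 8.8% v 13.6%: p̄ = 0.112; (1.960 × 0.4460 + 0.8416 × 0.4447)² / 0.048² = 676.4, so 677. Matches the plan.

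Power at these rates is 80.0% at both stages.

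**Step 3. Sample size for an exact 50% increase, same formula.**
- 11% v 16.5%: 614.2, so 615 per group (plan: 524).
- 8.8% v 13.2%: 792.6, so 793 per group, 1586 in total (plan: 677 and 1354).

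**Step 4. Power at the planned size for an exact 50% increase.**

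Power = Φ{[(p₂−p₁)√n − 1.960 × √(2p̄(1−p̄))] / √(p₁(1−p₁) + p₂(1−p₂))}

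- n = 677, 8.8% v 13.2%: (0.044 × 26.019 − 1.960 × 0.4425) / 0.4414 = 0.629, and Φ(0.629) = 73.5%.
- n = 677, control 11.5% diluted to 9.2%, v 13.8%: (0.046 × 26.019 − 1.960 × 0.4512) / 0.4500 = 0.695, and Φ(0.695) = 75.6%.
- n = 677, holding 17% and dividing by 1.5 (11.33% v 17%; diluted 9.07% v 13.6%): 74.9%.

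The result does not depend on the formula: the arcsine method gives 73.9% for 8.8% v 13.2% at n = 677. No reading of an exact 50% increase tried here reaches 80%.

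**The case against.** The strongest reply is that nothing was miscalculated. The sentence that says 50% also prints both rates, and the next steps print the diluted rates. The sample sizes follow exactly from those rates, so a careful reader can see which two proportions the trial is powered to separate. This stands. A reader might infer from the mismatch that the trial is underpowered or that 1354 is wrong. The documents do not support that, because for the effect given as rates the power is 80%.

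It can also be said that 50% is a round label. Both 1.5 × 11% = 16.5% and 1.5 × 11.5% = 17.25% round to 17%. Against 11%, 17% is a 54.5% increase; against 11.5% it is a 48% increase (17/11.5 = 1.478). Rounding is a plausible origin, and it is why the range above includes the 11.5% control rate. It does not remove the inconsistency, because the text equates the effect with 50% and then justifies that figure.

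A reader might also conclude that the effect is not conservative. That does not follow either. The claim rests on cited trials that are not at hand, and a 55% increase may be conservative against them. The one comparison in the Discussion with quit rates by arm, 13% versus 8% in a small trial of another app, is a 62.5% increase (13/8 = 1.625). That trial was small and had a different control, so it settles nothing, but nothing visible contradicts the claim.

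Finally, the label plays no part in the primary analysis, and a completed trial is judged by its estimate and confidence interval. This is fair, and it limits the consequence to how the design's power is described.

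**Conclusion.** The point holds as an inconsistency in how the effect is stated. The relative effect attached to 80% power is wrong as written: the powered effect is a 54.5% increase, and the justified one is 50%. The sample sizes of 524 and 677 per group are correct for the stated rates. For an exact 50% increase, 677 per group gives about 74% power at the planning control rate and about 76% at the cited 11.5%. Eighty percent power at the planning rate would need 793 per group.

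These figures assume that the 50% is a relative increase in the proportion abstinent, that 20% attrition applies equally to both arms with nonresponders counted as smokers, and that the comparison is the unadjusted two-sided test used for planning. Reading the 50% as an odds ratio of 1.5 would give 15.6% in the intervention arm, further from 17%. This is a correction of wording with a modest effect on stated power. It is not a defect in the design.

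**What to change.** Keep 1354. In Sample Size and Power Calculations:

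- State the powered effect as 17% versus 11%: 6 percentage points, about a 55% relative increase, and 4.8 points (13.6% versus 8.8%) once nonresponders count as smokers.
- Add that, with 677 per group, power for a 50% relative increase over the 11% planning rate is about 74%.
- Make the sentence that calls the effect reasonable and conservative refer to the effect actually powered, and check that the cited trials support it at that size.

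The cost is a few words and one slightly less favourable power figure. Recruitment, randomization, outcomes and analysis do not change.

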### Analysis Plan

#### Statistical Analysis

The intention-to-treat principle will be followed for statistical analyses and the imputation method for missing data will be conservative whereby nonresponders will be classified as smokers. Characteristics will be compared between the groups at baseline, at 3-month follow-up, and at 6-month follow-up using independent *t* tests for continuous variables, or chi-square tests for categorical variables as appropriate. Mann-Whitney U tests will be used where data are not normally distributed. Preliminary analyses using models appropriate for the distribution of the variables will be undertaken to determine variables that differ between treatment groups, and between those with complete and incomplete follow-up data. Any variables showing a significant difference will be used in models as covariates to adjust for imbalances between the groups.

The primary response variable—30-day abstinence at 6-month follow-up—will be analyzed in a logistic regression model with the treatment group as the main explanatory variable. Age, sex, and level of addiction will be included, as well as other covariates, to adjust for any differences between the groups. The coefficient for the treatment group will be tested at the 5% level using a likelihood ratio test. Evidence against the null hypothesis that the coefficient is zero will indicate a significant difference between the treatment groups, after adjustment for covariates that differ between the groups.

Secondary analyses that involve comparisons of 7-day abstinence, quit attempts, and consumption levels will be conducted using generalized linear models that consider the distribution of the response variable (eg, Poisson models for numbers of quit attempts) and special features of the data (eg, zero-inflated Poisson models for quit attempts, if necessary). Similarly, variables such as satisfaction, use of e-cigarettes, and use of cessation services will be modeled using generalized linear regression models that include the indicator variable for condition.

The Preacher and Hayes bootstrapping method will be used to provide point estimates and confidence intervals to assess the significance or nonsignificance of a mediation effect, as it provides an increase in power and does not require the normality assumption to be met [72]. The mediation analyses will proceed by first estimating the difference in the outcome variable between the treatment and control groups, adjusting for age and sex as necessary, and then estimating the difference between the conditions for the mediating variables using bootstrapping. Finally, mediating variables and the treatment group indicator, along with covariates, will be entered into models for the primary and secondary responses. This will allow for an investigation of the role the mediators play in accounting for the differences between conditions. For example, use of e-cigarettes, higher levels of dependence, lower levels of self-efficacy, and low perceived social support might mediate quit success, for example, lower quit rates (see Figure 3). Additional secondary analyses will look at models for the response variables involving a treatment group indicator, covariates, and interactions between covariates and the treatment group indicator. These models will examine whether the relationships between the outcome and covariates differ between the conditions. They will also help to identify potential mechanisms, for example, frequency of app usage, by which the intervention might be operating. Statistical analyses will be performed using SAS version 9.4.

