### Study Aims

The primary aim of this study will be to determine the effectiveness of the evidence-informed mobile phone app for smoking cessation, Crush the Crave, on reducing smoking prevalence among young adult smokers after 6 months. Crush the Crave was developed by an expert team based at the University of Waterloo who worked with a technology development team to design, prototype, evaluate, and revise the program over the course of 2 years. This study will represent the first full trial of the program as part of a population-level intervention. We expect that individuals randomized to the evidence-informed mobile phone intervention condition will have higher 30-day point prevalence quit rates than individuals assigned to the control condition after 6 months.

Secondary aims of this study include the following:

1. Examine more proximal outcome measures of cessation behavior, including 7-day point prevalence abstinence (PPA), time to cessation, the number of quit attempts, and the reduction in consumption of cigarettes.

2. Examine satisfaction and patterns of app use at 3 and 6 months, including the extent to which it promotes the use of established smoking cessation services, such as nicotine replacement therapy, health professional consults, medications, and quitline counseling.

3. Examine mediators of cessation outcomes between conditions, such as frequency of app use, use of cessation services, quit intentions, nicotine withdrawal, and the following psychosocial mediators: beliefs and attitudes, stress, social norms, self-efficacy, and perceived social support.

4. Compare the cost-effectiveness of the intervention and control conditions.

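### Primary-model covariates are selected by significance tests, so the model is not fixed in advance, and the wording does not confine the candidates to baseline

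*Protocol article*

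**What the plan says.** All of the rule stands in the Statistical Analysis section of the protocol article.

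- The comparisons cover three time points: "Characteristics will be compared between the groups at baseline, at 3-month follow-up, and at 6-month follow-up".
- Preliminary analyses are then run "to determine variables that differ between treatment groups, and between those with complete and incomplete follow-up data".
- The selection rule follows: "Any variables showing a significant difference will be used in models as covariates to adjust for imbalances between the groups".
- For the primary logistic model: "Age, sex, and level of addiction will be included, as well as other covariates, to adjust for any differences between the groups".
- The likelihood ratio test of treatment is read "after adjustment for covariates that differ between the groups".

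Three covariates (age, sex, level of addiction) are therefore named in advance. The others form an open set, filled by testing.

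Two other sections determine what could fall into that set. Questionnaire for 3- and 6-Month Follow-Up says: "Follow-up data will be collected from the same participants at 3 and 6 months in the same manner as the baseline questionnaire". It then adds items such as withdrawal, support received and services sought. Study Aims lists as a secondary aim: "Examine mediators of cessation outcomes between conditions, such as frequency of app use, use of cessation services, quit intentions, nicotine withdrawal", and goes on to psychosocial variables including self-efficacy and perceived support.

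**The concern.** There are two problems, and they differ in how firmly the text supports them.

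The first is plain from the text. Under randomization, a baseline difference between arms is a chance event. A covariate earns its place in the model by predicting abstinence, and a between-arm p-value does not measure that. The screen on completeness of follow-up can be run only once follow-up is in, so the covariate list for the primary test stays open until outcome data exist.

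The second is something the wording permits. The rule covers any variable, comes after comparisons at three time points, and carries no restriction to baseline. Level of addiction has no time point either, although dependence is measured at baseline, re-asked at follow-up, listed as a secondary outcome, and mentioned as a possible mediator. A variable that the app itself has changed is exactly one that would tend to differ between arms at 3 or 6 months. Entering it would remove part of the app's effect from the treatment coefficient. The test would then no longer address the primary aim, which is the effect of being assigned the app.

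**Working it through.** **1. The plan's own figure.** Inputs from Sample Size and Power Calculations: two-sided alpha 0.05, power 80%, 11% v 17% before attrition, 8.8% v 13.6% after 20% attrition.

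n per arm = [1.960·√(2·p̄·(1−p̄)) + 0.842·√(p₁(1−p₁) + p₂(1−p₂))]² / (p₂−p₁)²

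- 11% v 17%: (0.962 + 0.411)² / 0.06² = 524.
- 8.8% v 13.6%: (0.874 + 0.374)² / 0.048² = 677.

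Both match the plan. Power at 677 per arm is 80.0%. The sample size is not in dispute.

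**2. Would a shifted follow-up variable be selected?** For a shift of d SD with n per arm, the expected z is d·√(n/2). With d = 0.2 (assumed):

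- All 677 per arm followed up: 0.2·√338.5 = 3.68; probability of p < 0.05 = Φ(3.68 − 1.96) = 96%.
- 20% attrition, about 541 per arm: 0.2·√270.5 = 3.29; probability = Φ(1.33) = about 91%.

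**3. What would selection do to the primary test?** The document gives no mediator effect, so every d and b below is an assumption. Simulation: 677 per arm; a standard normal variable shifted by d SD in the app arm, with log-odds b per SD for abstinence; total rates held at 8.8% v 13.6%; the variable observed for everyone and entered only if its t test has p < 0.05; then a likelihood ratio test of treatment; 600 trials per row.

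| d (SD) | b | Selected | Power, unadjusted | Power under rule | OR, unadjusted | OR under rule |
|---|---|---|---|---|---|---|
| 0 | 0.8 | 4.5% | 78.5% | 78.8% | 1.63 | 1.63 |
| 0.2 | 0.5 | 95.7% | 81.2% | 62.3% | 1.64 | 1.51 |
| 0.2 | 1.0 | 95.0% | 82.0% | 44.7% | 1.63 | 1.41 |
| 0.3 | 0.8 | 100% | 80.7% | 38.2% | 1.65 | 1.34 |
| 0.3 | 1.0 | 100% | 81.5% | 28.8% | 1.66 | 1.30 |
| 0.5 | 1.0 | 100% | 80.7% | 6.7% | 1.64 | 1.05 |

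In the last row almost the whole effect runs through the mediator (remaining direct log-odds 0.042), so it marks the extreme of the range.

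**4. Nonresponders.** The plan counts them as smokers. At 20% attrition that is 0.20 × 1354 = about 271 people without 6-month covariate values. An ordinary logistic fit containing such a covariate would drop them.

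**5. Baseline-only screening.** The chance of at least one false selection among k independent items at 5% is 1 − 0.95^k: 40% for k = 10 and 64% for k = 20, with 0.5 and 1.0 selections expected. Simulated type I error with 10 baseline candidates screened between arms (4000 trials per setting) was 4.9% and 5.1%, against 5.1% and 5.4% unadjusted. This simulation did not include the completeness-of-follow-up screen.

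**The case against.** A reader might infer that the plan prescribes adjusting the primary test for mediators. The document does not say so, and several points suggest that baseline was meant.

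- The three-time-point comparisons and the covariate rule are separate sentences, and the stated purpose is to correct imbalance, a term that normally refers to baseline.
- The mediation paragraph treats mediators and covariates as different classes. Mediators enter only in its last step, after a first step that adjusts for age and sex as needed.
- Use of cessation services, satisfaction and e-cigarette use are modelled as responses to condition.
- Counting nonresponders as smokers fits poorly with 6-month covariates that they do not have.

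This stands as evidence of intent, and it is why the mediator point is put here as something not excluded. It does not close the gap: no sentence keeps follow-up variables out of the primary model.

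Three further inferences go too far. Inflated type I error from baseline screening is not supported by the simulation. A contradiction with Randomization and Blinding, which holds that "the likelihood is remote that, by chance, the two study groups may not be well matched for baseline characteristics", is weak: one nominally significant item among many is not poor matching. Free choice of model after unblinding is also weak, because the rule is mechanical and investigators and data collectors stay blinded until the trial is complete.

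Finally, a fuller covariate list is often left to an analysis plan. Here, however, the article states a selection rule outright, so the point is about a rule fixed badly and not about missing detail.

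**Conclusion.** The concern holds in two parts. What the text establishes is that covariates beyond the three named ones are chosen by significance tests, partly on completeness of follow-up. The primary model is therefore not fixed before outcome data exist, and it selects on chance difference. If candidates are limited to baseline, the demonstrated harm is an unfixed model: a 40% to 64% chance of at least one chance selection, on the assumption of 10 to 20 independent items (the actual items are related), with type I error near 5%.

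What the wording leaves open is the entry of follow-up variables, including an undated level of addiction. If that happened, the estimand would become a partial direct effect. Power would fall from about 80% to between 62% and 7%, and the odds ratio from about 1.64 to between 1.51 and 1.05. Those ranges rest entirely on assumed shifts of 0.2 to 0.5 SD and log-odds of 0.5 to 1.0 per SD. With no shift, nothing changes. They show what is at stake if the rule is followed literally and do not forecast the trial's result.

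**What to change.** In Statistical Analysis:

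1. Specify the primary model as treatment plus baseline age, sex and nicotine dependence, with baseline cigarette consumption if wanted. State that the level of addiction is the baseline value.
2. Drop both significance screens, between arms and between those with complete and incomplete follow-up, as rules for choosing covariates.
3. State that no variable measured after randomization enters an effectiveness model. Keep such variables to the mediation analysis already planned.
4. Label any model with further baseline covariates as a sensitivity analysis.

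The cost is a few sentences in the plan. No data collection, sample size or participant is affected, and the planned 80% power is kept.
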